#### Intended Sample Size

Based on comparable studies with a 95% confidence level, 80% power of the test, variance of 0.0036 units, and an accuracy (improvement) of 0.06 units in the PCC, each group requires a maximum sample size of 16 participants.

### Ethical Considerations

Participants’ safety risk will not be increased by participating in this trial. Each participant’s information will be stored under a unique number, and the coded information will be appropriately stored. When the research is completed, the results will be presented at scientific conferences or published in scientific journals, and the identities of study participants will remain confidential. The parents will be required to complete the informed consent form before participating in the study, and both the researcher and the participant must sign the document, with a copy provided to the participant. This study has been approved by the Research Ethics Committee of the University of Social Welfare and Rehabilitation Sciences, Iran (IR.USWR.REC.1400.310).

## Results

The protocol was approved by the Research Ethics Committee of the University of Social Welfare and Rehabilitation Sciences in February 2022. The selection process of participants, training therapists, and raters, commenced in January 2022, the therapy and follow-up periods ended in June 2023, and pre- and postintervention assessments have been conducted. Data analysis is ongoing, and we expect to publish our results by the summer of 2024. Funding is yet to be obtained.

## Discussion

This study is the first RCT with follow-up, which aims to develop a protocol to evaluate the effect of parent-based EMT+PE through telepractice in Persian-speaking toddlers with nonsyndromic cleft palate.

In this study, the impact of the interventions will be evaluated by language and speech outcomes as primary outcome measures. Language outcomes include a vocabulary inventory, collected using the MCDI, mean length utterances, number of total words, and number of different words, collected through language samples and during the parent-child interaction. Speech outcomes including PCC, consonant inventory, whole-word accuracy match, and whole structure match will be collected during the PEEPS assessment. The effect of interventions will be examined for 12 weeks, with an additional 8-week follow-up period for the EMT+PE group to exclude any temporary effects that may have limited clinical value. Our results will provide information about the efficacy of the parent-implemented EMT+PE telepractice intervention in enhancing speech skills while also promoting speech production and language measures and its stability over a prolonged period. In addition, we will obtain parents’ satisfaction and score on the Intelligibility in Context Scale before and after delivering interventions as secondary outcome measures. Improvement of speech intelligibility is a long-term target of most speech therapy interventions.

The study’s limitations include its small sample size for each age group. To address the effects of such interventions, a larger-scale clinical trial is necessary. Additionally, the intervention and follow-up periods are limited in demonstrating effects. It is important to note that toddlers are in different age ranges and may require more time to develop their language and speech skills.

In summary, we anticipate demonstrable effects of the parent-implemented EMT+PE telepractice intervention on language and speech outcomes in toddlers with CP/L; these should specifically include not only an extended vocabulary inventory but also an improved consonant inventory and speech intelligibility. This study’s results may help develop a specific intervention with a different delivery model for toddlers. Parent training through telepractice has multiple benefits for families, including providing therapy for children with speech-language disorders, reduced costs, unrestricted access to therapy services for people living in rural areas, and saving time and expenses [24-26]; therefore, cleft care teams can harness our results in service delivery.

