**Objective:**

This study aims to determine and compare the effectiveness of telepractice and the parent-implemented EMT+PE intervention on language and speech measures in toddlers with CP/L with usual interventions and determine the effectiveness maintenance of the intervention.

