**Methods:**

A randomized controlled trial (RCT) will assess the efficacy of telepractice and the parent-implemented EMT+PE intervention in enhancing speech and language measures in toddlers with CP/L. Eligible participants will be randomly assigned to one of 2 groups: the conventional intervention group and the EMT+PE intervention group. Participants’ speech and language measures will be evaluated remotely by trained raters before and after the intervention and 2 months after the intervention. Parents of participants in the intervention group will receive 3 months of training in speech and language supportive strategies from trained therapists using telehealth fidelity scales. Parents of participants in the control group will receive the conventional speech and language intervention by cleft team therapists. Study outcomes will include language variables (mean length of utterance) and speech production variables (percent correct consonants).

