#### Secondary Objectives

Our secondary objectives are to compare the effectiveness of this parent-based telepractice EMT+PE intervention with usual-care interventions and determine the effectiveness of the intervention in the follow-up period.

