#### Usual-Care Intervention

Children assigned to the usual-care intervention (control) group will be assessed twice before and after the 3-month intervention. If they are not, they will be enrolled in cleft teams. They will receive speech and language therapy there in accordance with a specific protocol. Regular evaluations administrated every 3-6 months, are part of the usual speech and language intervention for children aged up to 3 years undergoing team care. Based on each child’s evaluation, early counseling is provided to parents in person or remotely. Parents are expected to apply the recommendations provided until the next visit. The EMT+PE will not be administered to participants in the control group throughout the experimental intervention period.

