### Data Collection

In total, 32 children with CP/L in different provinces of Iran (Isfahan, Tehran, and Shiraz) who meet the primary inclusion criteria will be recruited. Next, the first author will call the parents and explain the process and the study’s terms of acceptance. Then, she will schedule a web-based session to complete the assessment. Parents will complete demographic information forms followed by the Age and Stages Questionnaire for their children’s developmental screening. Parents will collect speech and language samples before and after the intervention for their child in the naturalistic environment (Multimedia Appendix 3).

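### The article contradicts itself on whether controls are assessed at 2 months; if they are not, the follow-up cannot rule out a temporary effect or show a lasting advantage over usual care

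*Protocol article*

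**What the plan says.** Four places in the article describe the assessment schedule.

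- **Abstract, Methods.** It names the two randomised groups and then says that participants' "speech and language measures will be evaluated remotely by trained raters before and after the intervention and 2 months after the intervention". No arm is singled out.
- **Usual-Care Intervention.** "Children assigned to the usual-care intervention (control) group will be assessed twice before and after the 3-month intervention". No 2-month visit is mentioned.
- **Discussion.** After the 12-week period there is a further stage, "with an additional 8-week follow-up period for the EMT+PE group to exclude any temporary effects that may have limited clinical value".
- **Data Collection.** "Parents will collect speech and language samples before and after the intervention for their child in the naturalistic environment". No follow-up sample is named for either arm.

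Lasting effect is a stated aim. The abstract's Objective includes to "determine the effectiveness maintenance of the intervention", and Secondary Objectives includes to "determine the effectiveness of the intervention in the follow-up period". The Discussion also expects the results to speak to how stable the gains are over a longer time. Statistical Analysis plans between-group differences with a 95% CI, ANCOVA, and a paired t test within a group. It does not tie any of these to the 2-month visit.

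**The concern.** Two things are wrong. First, a reader cannot tell from the text which design was run at 2 months: two arms or one. Second, if only the EMT+PE arm was followed, the purpose given for the follow-up goes beyond what it can deliver. An effect is temporary, or not, relative to what would have happened without the intervention. Without controls at 2 months, that reference is missing in children whose speech and language are still developing. Controls might also catch up without anyone seeing it.

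At stake are a secondary objective and the Discussion's promised conclusion about stability. A flat or rising EMT+PE score could be reported as a lasting benefit when the difference from usual care has shrunk or gone.

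**Working it through.** **1. The statements side by side**

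| Place | EMT+PE at 2 months | Control at 2 months |
|---|---|---|
| Abstract, Methods | yes | yes, on the natural reading |
| Usual-Care Intervention | not addressed | no: two assessments, before and after |
| Discussion | yes (8 weeks) | no: follow-up given to EMT+PE |
| Data Collection | not mentioned | not mentioned |

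The Usual-Care sentence is loosely worded, but the Discussion supports the plain reading of one assessment before and one after. These two places agree with each other and conflict with the abstract.

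**2. What can be estimated under the one-arm version**

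For one child, let G be the ordinary development over the 8 weeks and L the part of the intervention effect lost over the same time.

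- Expected change in EMT+PE = G − L.
- Expected change in control, if measured = G (plus any catch-up).
- The difference between arms isolates the loss of advantage. The EMT+PE change alone does not, because G and L cannot be separated.

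The documents give no figure for G. The table takes the planned effect of 0.06 in PCC from Intended Sample Size and assumed values of G.

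| Loss L | G = 0 | G = 0.02 | G = 0.03 | G = 0.06 |
|---|---|---|---|---|
| 0 (fully kept) | 0.00 | 0.02 | 0.03 | 0.06 |
| 0.03 (half lost) | −0.03 | −0.01 | 0.00 | 0.03 |
| 0.06 (all lost) | −0.06 | −0.04 | −0.03 | 0.00 |

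An observed change of 0.00 fits an effect fully kept, half lost or wholly lost, depending only on G. More children in the same single arm would not resolve this.

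That G is not zero is plausible from the article itself. Entry age is 18 to 36 months, and the Discussion's limitations concede that the children may need further time for their language and speech to develop.

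**3. What a control visit would provide**

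The stated sample size reproduces. With SD = √0.0036 = 0.06, difference 0.06, two-sided α 0.05 (sidedness assumed) and 80% power:

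n per group = 2 × (1.960 + 0.842)² × 0.0036 / 0.06² = 2 × 7.85 = 15.7, rounded up to 16.

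With 16 v 16 measured at 2 months, no dropout and the same variance, power for a 0.06 difference is 0.807 by the normal approximation and 0.781 by the noncentral t distribution. A two-arm follow-up would therefore keep roughly the planned precision without more children.

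**The case against.** **What stands.** Figure 1 and the study timeline in Multimedia Appendix 3 are not shown and may give the schedule by arm. They could settle which version applied, but they would not remove the conflict in the text. The abstract is a condensed summary. The affected objective is secondary. The limitations also admit that the intervention and follow-up periods restrict what can be demonstrated, although they do not name the missing control. Finally, Secondary Objectives lists the comparison with usual care and the follow-up as separate items, so the follow-up item is not itself worded as a between-arm question. A one-arm follow-up can properly describe whether EMT+PE scores fall after training stops.

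**Stronger readings that the documents do not support.**

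- A reader might infer that the abstract promises follow-up of every participant. It does not say so; it only sets no limit by arm after naming both groups.
- A reader might infer that a non-significant paired test between the post-intervention and follow-up visits will be taken as proof of maintenance, and might attach an error rate to that rule. Statistical Analysis states no such rule and does not say which visits the paired test compares. Any such rate would also need a between-visit correlation that the article does not give and an assumption of no development, so none is offered here.
- A reader might infer that the follow-up is worthless or that the trial's main result is compromised. Neither follows.

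**Conclusion.** The point holds in a limited form. The text contradicts itself on whether controls are assessed at 2 months. Under the Usual-Care and Discussion version, no between-arm estimate exists at that time. The within-arm change then cannot exclude a temporary effect or establish that the benefit over usual care is stable.

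This rests on the design alone. It needs only that some ordinary development over 8 weeks is possible in this age group. The values of G above are assumptions that illustrate how far the change could mislead; they are not estimates of bias in this trial. The randomised comparison after the 3-month intervention is untouched.

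**What to change.** Reconcile the Abstract (Methods), Usual-Care Intervention and Discussion, and state which arms were assessed at 2 months. The Results section says follow-up ended in June 2023 with analysis still under way, so the remedy depends on what was collected.

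- **If control data at 2 months exist:** correct the Usual-Care Intervention and Discussion sections. Report the between-arm difference at 2 months from the ANCOVA already planned, adjusted for baseline, with a 95% CI. Cost: wording and one further analysis.
- **If they do not exist:** correct the abstract and delete the Discussion's clause about excluding temporary effects. Relabel the follow-up aim in the abstract's Objective, Secondary Objectives and Discussion as an uncontrolled description in the EMT+PE arm. Report the change from post-intervention to follow-up with a 95% CI, and make no claim that effectiveness over usual care was maintained. Cost: wording and a narrower secondary claim.

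Neither route needs new data or alters the 3-month analysis.

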## Appendix

Multimedia Appendix 1 Telehealth Fidelity Scales.

Multimedia Appendix 2 EMT+PE Fidelity Rating Form. EMT+PE: Enhanced Milieu Teaching with Phonological Emphasis.

Multimedia Appendix 3 Study timeline.

## Abbreviations

CLP: cleft lip and palate
CONSORT: Consolidated Standards of Reporting Trials
CP/L: cleft palate with or without cleft lip
dB HL: decibels in hearing level
EMT: Enhanced Milieu Teaching
EMT+PE: Enhanced Milieu Teaching with Phonological Emphasis
MCDI: Macarthur-Bates Communicative Development Inventory
PCC: percentage of correct consonants
PE: Phonological Emphasis
PEEPS: Profiles Of Early Expressive Phonological Skills
RCT: randomized controlled trial
SLP: speech-language pathologist
TMCR: Teach-Model-Coach-Review
